## 5.5 Clinical performance panel

- Left-over whole blood or serum submitted for routine testing can be used to evaluate the assays. Clinical specimens should be stored frozen at -20°C or preferable -80°C when available until testing. Total 100 specimens: 10 spiked with 5000 ge /mL of the African wild strain, 10 spiked with 5000 ge /mL of the South American wild strain and 80 non-reactive specimens will be tested.

## 5.6 Criteria for eligible specimens

- Specimens will be eligible for the evaluation study if they have a sufficient volume of ca. 1 mL serum to perform the assay under evaluation after all standard of care testing, including reference standard. The specimen must be of a type validated as suitable for use for the candidate assay.

### Table 1: Assay Performance Specimen Reference Panel

| **Analyte - Sample type** | **Concentration (copies/mL)** | **N° of replicates** | **Total N° replicates** |
| --- | --- | --- | --- |
| **Precision of measurement and inclusivity** |  |  |  |
| **Intra-assay precision/inclusivity** |  |  |  |
| YF 17D vaccine strain* | Each strain will be diluted at a concentration of ca. 10^3^, 10^4^ and 10^5^ ge copies /mL and run in quadruplicate | 3 | 12 |
| African wild type strain* |  | 3 | 12 |
| South American wild type strain* |  | 3 | 12 |
| **Inter-assay precision** |  |  |  |
| YF 17D vaccine strain* | Each strain will be diluted at a concentration of ca. 10^3^, 10^4^ and 10^5^ ge copies /mL and run in quadruplicate on 3 different days by different technicians (day 1 can use intra-assay data) | 3 | 24 |
| African wild type strain* |  | 3 | 24 |
| South American wild type strain* |  | 3 | 24 |
| **Inter-lot variability** |  |  |  |
| YFV 17D vaccine strain* | Each strain will be diluted at a concentration of ca. 10^3^, 10^4^ and 10^5^ and run in quadruplicate | 3 | 12 |
| YFV African wild type strain* |  | 3 | 12 |
| YFV South American wild type strain* |  | 3 | 12 |
| **Analytical Sensitivity** | | | |
| YFV Standard preparation* | ca. 10, 50, 100, 500, 1000, 5000, 10^4^, 5x10^4^, 10^5^, 5x10^5^, 10^6^ , 5x10^6^ ge copies /mL** | 5 | 25 |
| **Analytical Specificity (**Flavivirus strain detection) | | | |
| Hepatitis C* virus | Medium concentration  ca. 10,000 ge copies/mL | 1 |  |
| Dengue 1, 2, 3, 4*virus |  | 1 |  |
| Zika virus* |  | 1 |  |
| West Nile virus* |  | 1 | 9 |
| Tick Borne Encephalitis virus* |  | 1 |  |
| Japanese Encephalitis virus* |  | 1 |  |
| **Analytical Specificity (other pathogens)** | | | |
| Ebola virus* | medium concentration  ca. 10,000 ge copies/mL | 1 |  |
| Lassa fever virus* |  | 1 |  |
| Marburg virus* |  | 1 |  |
| HIV* |  | 1 | 8 |
| Hepatitis E virus* |  | 1 |  |
| Chikungunya virus* |  | 1 |  |
| Measles virus* |  | 1 |  |
| Influenza virus* |  | 1 |  |
| **Analytical Specificity (interfering substances)** | | | |
| Haemoglobin | 200 g/L | 3 |  |
| Triglyceride | 5.6 mmol/L | 3 | 12 |
| Bilirubin (unconjugated) | 257 µMol/L | 3 |  |
| Malaria positive sera |  | 3 |  |
| **Clinical Performance Panel** | | | |
| Non-reactive serum specimens Spiked African wild type | 5000 ge copies/ mL | 10 | 10 |
| Non-reactive serum specimens Spiked South American wildtype | 5000 ge copies/ mL | 10 | 10 |
| Non-reactive serum specimens |  | 80 | 80 |
| Total number of samples to be | tested |  | 305 |

ge = genome equivalent

* A inactivated YF prototypevirus grown in cellculture should be used for this evaluation.

All specimens will be prepared in concentrations representing the dynamic range of the assay under evaluation.

**Five of these dilutions will be chosen where the manufacturer’s LoD is approximately the middle dilution

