# 5. Specimen Panels

## 5.1 Specimen types

All panels will be prepared using the specimen type/s indicated in the NAT’s instructions for use. Where multiple specimen types are identified, serum will be the preferred specimen type. The clinical specimens will be serum collected from an endemic setting during a non-outbreak period. Where possible, specimens should be collected from patients with symptoms similar to those seen in YF.

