## 5.4 Analytical Performance Specimen Reference Panel

Reference Panel preparation consists of cell culture-grown YF strains (17D YF vaccine strain, prototype African wild type strain, prototype South American wild type strain) diluted in YF negative serum.

The YF 17D standard preparation (RKI / European Virus Archive (EVA), <https://www.european-virus-archive.com/node/2495>) could be used as 17D reference material. Also the EQA YF Virus 195 panel from QCMD could be used as reference material. This panel comprises YFV 17D in different concentrations, Japanese encephalitis, West Nile, Zika, and Dengue 2 viruses for analysing the assay specificity.

- Precision of measurement:
- Three specimens representing the most relevant YFV strains (17D YFV vaccine strain, African wild type strain, South American wild type strain) will be used. Each YFV-positive specimen will be diluted in serum which has been tested negative for HIV, HBV and HCV to obtain a concentration of ca. 5000 ge copies / mL of the assay.
- Inclusivity:
- Specimens to demonstrate appropriate YF strain detection. They should comprise at least the 17D YFV vaccine strain, an African wild type strain and, a South American wild type strain. These specimens will be diluted to a concentration of 5000 ge copies/mL of the assay.
- Assessment of the Analytical sensitivity:
- The YFV 17D standard preparation from RKI will be used to prepare five-fold serial dilutions in YFV-negative serum comprising at least two concentrations at 5000 ge copies /mL, one concentration at 1000 ge copies /mL and two concentrations at 500 and 100 ge copies/ mL (Tab. 1)
- Analytical Specificity
- Non-YFV flavivirus strains and other pathogens (except malaria). Testing will be conducted with cell culture preparations of the various viruses (using prototype strains) spiked into negative serum specimens. Each virus will be spiked at concentrations found in clinical presentations.
- Interfering substances.
- Testing will be conducted with YFV 17D standard preparation at a concentration of ca. 10^3^ ge copies/mL spiked with challenging sera (see Table 1) in order to detect potential interference for the assays under evaluation. The malaria specimens will be those identified as positive by microscopy.

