## 6.3 Analytical Specificity

For the evaluation of possible interfering substances for the assay performance different sera (malaria positive, lipaemic, hemolytic sera, see Table 1) will be spiked with ca.10,000 ge copies/mL 17D YF standard preparation. Tests should be performed in triplicate.

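### Table 1 sets the haemoglobin interferent at 200 g/L, above assumed whole-blood levels, although the challenge is described as haemolytic serum; value, unit and source need confirming

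*Protocol*

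**What the plan says.** The interfering-substances block of Table 1 has four rows of three replicates each, 12 tests in all. Three rows carry a concentration: "Haemoglobin | 200 g/L", "Triglyceride | 5.6 mmol/L" and "Bilirubin (unconjugated) | 257 µMol/L". The fourth, malaria-positive sera, has none.

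Two sections describe the material. Section 5.4 has the 17D preparation "spiked with challenging sera (see Table 1) in order to detect potential interference for the assays under evaluation". Section 6.3 names the sera as "malaria positive, lipaemic, hemolytic sera, see Table 1" and asks for triplicate testing.

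On matrix, section 5.1 ties the panels to the specimen types in the assay's instructions and adds: "Where multiple specimen types are identified, serum will be the preferred specimen type". Whole blood as test material appears in section 5.5, for the clinical panel: "Left-over whole blood or serum submitted for routine testing can be used to evaluate the assays".

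The protocol gives no source or rationale for any interferent level, no second haemoglobin figure, and no pass/fail limit for interference.

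**The concern.** Haemolysed serum is serum contaminated by the contents of some lysed red cells. It should not hold more haemoglobin than the blood it was drawn from, so a serum challenge set above whole-blood haemoglobin is out of line with its own description.

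Section 4 presents the evaluation as risk-based and focused on what matters when the tests are used in Member States, and section 4.3 names endogenous interfering substances as a characteristic to be assessed. Section 8.3 wants each analyte reported separately and unexpected results noted. An assay inhibited at 200 g/L would therefore have that finding in its report, and a reader would take it as information about haemolysed field specimens, which it would not be.

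**Working it through.** **Inputs from the protocol (Table 1):** haemoglobin 200 g/L; triglyceride 5.6 mmol/L; unconjugated bilirubin 257 µmol/L; four interferents with three replicates each.

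**Assumed inputs (not in the protocol):** whole-blood haemoglobin 110-180 g/L; haemoglobin inside red cells 300-360 g/L; molar mass of triglyceride 850-900 g/mol (885.4 as a central value) and of bilirubin 584.66 g/mol.

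**Step 1, the protocol's own count.** 4 interferents × 3 replicates = 12, which agrees with Table 1. Haemoglobin accounts for 3 of the 12. The 200 g/L itself is entered directly, so there is no derivation to reproduce.

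**Step 2, against whole blood.** Ratio = 200 / whole-blood haemoglobin.
- At 180 g/L: 200/180 = 1.11
- At 150 g/L: 200/150 = 1.33
- At 110 g/L: 200/110 = 1.82

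The entry stops exceeding fully lysed whole blood only if whole blood is taken to hold 200 g/L or more.

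**Step 3, what the specimen would consist of.** Share of lysed packed cells by volume = 200 / red-cell haemoglobin.
- At 360 g/L: 200/360 = 56%
- At 300 g/L: 200/300 = 67%

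More than half of the specimen would be lysed cells, so it would no longer be mainly serum. For comparison, 2 g/L would need 2/360 to 2/300, about 0.6-0.7%.

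**Step 4, the neighbouring rows in mg/dL.**
- Triglyceride: 5.6 mmol/L × molar mass / 10. This gives 5.6 × 850/10 = 476, 5.6 × 885.4/10 = 496 and 5.6 × 900/10 = 504 mg/dL.
- Bilirubin: 257 µmol/L × 584.66 / 10,000 = 15.0 mg/dL.

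Both are close to round values (500 and 15), as would be expected if the list had been built in mg/dL and then converted.

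**Step 5, the size of a possible slip.** 1 g/L = 100 mg/dL, so 200 g/L = 20,000 mg/dL and 200 mg/dL = 2 g/L. If 200 mg/dL was intended, the entry is 200/2 = 100 times too high. The factor is exact but depends wholly on that condition.

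**The case against.** **No error is documented.** The protocol nowhere gives 200 mg/dL, 2 g/L or a source. The unit-slip argument rests on two rows and outside molar masses. If the list did start in mg/dL, those two rows were converted correctly, so a failed conversion in the third is possible but not shown. A different slip would give a different factor, and a deliberate worst case would mean no slip at all. This stands: 100-fold can only be a conditional figure.

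**The material can be made.** Section 1.2 says the panels are artificially prepared, and step 3 shows that 200 g/L is reachable with enough lysed cells. This also stands. The complaint is not that the challenge is impossible, but that it does not represent what section 6.3 describes.

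**Whole blood may be the reference.** Section 5.1 follows the assay's instructions, Annex 1 (item 8) lists whole blood as a possible specimen type, and a level just above whole-blood haemoglobin might serve as an upper bound. This does not fit the text: sections 5.4 and 6.3 both describe sera, and section 5.5 admits whole blood for the clinical panel only.

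**The consequence is limited.** Too high a level makes the test stricter, so an assay that passes has shown more. If Table 1 is followed, all assays face the same challenge. The only criterion explicitly tied to listing is the LoD of at most 1000 ge copies/mL in section 8.3. All of this stands and limits the weight of the point. It does not help to interpret a failure at 200 g/L, which would say little about haemolysed serum.

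**Conclusion.** The haemoglobin level in Table 1 does not fit the matrix described in sections 5.4 and 6.3. On the assumed range of 110-180 g/L it is 1.1 to 1.8 times fully lysed whole blood. It governs 3 of the 12 interference tests for every assay, and any error makes the challenge too harsh rather than too lenient.

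Two stronger readings are tempting. A reader might infer that the entry is a proven 100-fold unit error. The neighbouring rows make a slip likely, but no value in mg/dL and no source is given, so this stays an inference. A reader might also infer that an assay could be wrongly refused listing. The protocol attaches no pass/fail rule to interference, so that does not follow. Nor is the mix of g/L, mmol/L and µmol/L a fault in itself.

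The conclusion rests on the assumed whole-blood range and fails only at 200 g/L or above.

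**What to change.** Before testing starts, check the haemoglobin value and its unit against the source from which the interferent levels were taken. Correct Table 1 to a level attainable in haemolysed serum, so that it agrees with section 6.3; if the source says 200 mg/dL, the entry becomes 2 g/L. If 200 g/L is a deliberate worst case, state that with its rationale and label the result in the report as a worst-case challenge, not as evidence on ordinary haemolysed specimens. Citing the source beside the entry would settle the question for later readers.

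The cost is one table entry, or one sentence of justification. The number of tests does not change.

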# 6. Laboratory testing

## 6.1 Review of the instructions for use

Each product under evaluation will be used in accordance with manufacturer instructions. The evaluating laboaratory will send a copy of the instructions to WHO together with the evaluation report. Records of the instructions must be maintained as part of the evaluation report used must be kept.

**6.2 Analytical Performance Testing**

The determination of precision and inclusivity will be undertaken in a single set of experiments.

- Four specimens will be used: one YF negative, one YF 17D, one YF African wild type, and one YF South American wild type, at a concentration of 10^3^-10^5^ ge copies /mL, (see Table 1).
- Intra-run variability (repeatability): The same sample panel (ca.10^3^, 10^4^, 10^5^ ge copies/mL) should be tested on the same run. Each panel member should be tested in quadruplicate.
- Inter-run variability (reproducibility): The same sample panel (ca. 1000, 10^4^, 10^5^ ge copies/mL) should be tested in 3 different runs preferably by different technicians.Each panel member should be tested in quadruplicate on each run.
- Inter-lot variability: The same sample panel (ca.10^3^, 10^4^, 10^5^ ge copies/mL) should be tested on a second lot of the product. Tests should be performed in quadruple.

Results should not vary by more than 3 ct values, by frequent performance in the same laboratory.

Twelve concentrationss of YF 17D standard preparation, diluted as described in Table 1, will be tested 5 times. The 5 replicates will be separated in a minimum of three runs where applicable.

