## 8.3 Analytical Sensitivity and Specificity

The limit of detection (LoD) is the lowest concentration of analyte that can be consistently detected in at least 95% of specimens tested under routine laboratory conditions and in a given specimen matrix. It defines the analytical sensitivity. The sensitivity and LoD will be estimated using the Probit analysis on the results of the five replicates of the LoD panel.

An acceptance criteria for the lower performance limit of the assay shall be ≤1000 ge copies/mL. Assays that do not reach this LoD will not be considered for listing by the WHO.

The results of testing for each individual analyte should be reported separately. Where unexpected results have been encountered, these should be noted in the report

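### The protocol gives two different sizes for the limit-of-detection panel (twelve levels or five), and a minimum list that some five-level panels cannot meet; the choice decides whether the probit LoD can be estimated

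*Protocol*

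**What the plan says.** Three places in the protocol describe the 17D panel used to estimate the LoD.

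- **Section 5.4** calls for "five-fold serial dilutions in YFV-negative serum comprising at least two concentrations at 5000 ge copies /mL, one concentration at 1000 ge copies /mL", together with 500 and 100 ge copies/mL, and refers to Table 1.
- **Table 1** lists twelve candidate levels from 10 to 5x10^6 ge copies/mL, with 5 replicates and a row total of 25. Its footnote reads "Five of these dilutions will be chosen where the manufacturer’s LoD is approximately the middle dilution".
- **Section 6.2** reads "Twelve concentrationss of YF 17D standard preparation, diluted as described in Table 1, will be tested 5 times".

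Section 8.3 uses the data as follows: "The sensitivity and LoD will be estimated using the Probit analysis on the results of the five replicates of the LoD panel". It sets an acceptance limit of 1000 ge copies/mL and says that assays that do not reach it will not be considered for listing. Table 1 gives an overall total of 305 samples; section 10 estimates 310 tests. No section says which description of the panel prevails.

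**The concern.** Five levels and twelve levels are different experiments, and every assay meets this conflict. The 5.4 list is a further complication. Stepping down five-fold from 5000 gives 5000, 1000, 200, 40, 8, not 5000, 1000, 500, 100. A five-level panel centred on 100 or below (10, 50, 100, 500, 1000) omits 5000 and so breaks the 5.4 minimum.

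A probit LoD needs levels at which some replicates are detected and some missed, with overlap between levels. If the levels run all the way to the upper end of detection, there is no finite fit. Two operators following different sections could therefore obtain an LoD from one panel and none from the other, for the same assay. The probit LoD is the only result with a stated listing consequence, and verifying claimed LoDs is one of the objectives in section 2.2.

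**Working it through.** **1. Test counts.** Five levels x 5 replicates = 25, which reproduces the Table 1 row. Twelve x 5 = 60, which does not; the difference is 35.

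**2. Overall totals.** The other Table 1 rows are intra-assay 36, inter-assay 72, inter-lot 36, flaviviruses 9, other pathogens 8, interfering substances 12 and clinical panel 100, together 273. With 25 LoD tests the sum is 298; with 60 it is 333. Neither equals 305 or 310.

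**3. Fit of the 5.4 minimum with the other two.** Its four distinct levels (5000, 1000, 500, 100) are all among the twelve. They are also all in the five-level panels centred on 500 (50 to 5000) and on 1000 (100 to 10^4). They are not all in the panel centred on 100 (10 to 1000).

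**4. Probability that a finite probit fit exists.** The protocol gives no detection curve, so I assume single-hit detection, p(c) = 1 - 0.05^(c/LoD), which gives 95% at the LoD. A finite fit requires a missed replicate at a higher level than some detected replicate. There are 5 replicates per level (10 at 5000 for the 5.4 list).

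True LoD 200, 5.4 minimum levels: a miss is needed at 500 or above. At 500 the miss probability is 0.05^2.5 = 0.00056 per replicate, so the chance of any miss in five is about 5 x 0.00056 = 0.0028, or 0.3%. Misses at 1000 and above are negligible. The panel centred on 1000 gives the same result.

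True LoD 200, levels 10 to 1000: write A10 and A50 for all five missed at 10 and at 50, H50 and H100 for all five detected at 50 and at 100.
- A10 = 0.05^0.25 = 0.473; A50 = 0.05^1.25 = 0.024
- H50 = (1 - 0.05^0.25)^5 = 0.041; H100 = (1 - 0.05^0.5)^5 = 0.282

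With everything detected at 500 and above (probability 0.997), the patterns without a fit are:
- all detected at 50 and 100: 0.041 x 0.282 = 0.011
- all missed at 10, not all detected at 50, all detected at 100: 0.473 x 0.959 x 0.282 = 0.128
- all missed at 10 and 50, not all detected at 100: 0.473 x 0.024 x 0.718 = 0.008

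The sum is 0.147, so a fit exists in about 85%. Adding the seven levels from 5000 upward does not change this.

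Exact results by the same method:

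| True LoD | 5.4 minimum | Table 1, claim 1000 (100 to 10^4) | Table 1, claim 500 (50 to 5000) | 10 to 1000 | All twelve |
|---|---|---|---|---|---|
| 100 | 0% | 0% | 22.6% | 65.7% | 65.7% |
| 200 | 0.3% | 0.3% | 70.2% | 85.3% | 85.3% |
| 500 | 22.5% | 22.5% | 81.6% | 86.3% | 86.3% |
| 1000 | 65.7% | 65.7% | 83.8% | 86.0% | 86.0% |

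**5. Sensitivity to the assumed curve.** With probit curves of SD 0.4 and 0.6 log10 and a true LoD of 200, the 5.4 minimum gives 2 to 6%, against 72 to 83% on 10 to 1000 or on all twelve levels. With slopes of 1.5 to 4 per log10 at LoD 500, the ranges are 12 to 30% (5.4), 16 to 87% (claim 500) and 16 to 94% (twelve). At the steepest slope the panels nearly converge (12% against 16%).

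**The case against.** **Section 5.4 sets a minimum.** A reader might infer that 5.4 fixes four levels for every assay, so that the protocol holds three mutually incompatible panels. The text does not support that. It says "comprising at least two concentrations at 5000 ge copies /mL, one concentration at 1000 ge copies /mL and two concentrations at 500 and 100", which is a floor, and it points to Table 1. Its levels can be met within the twelve, and within five levels centred on 500 or 1000. The conflict that always applies is five against twelve; for claims at or below the limit, 5.4 clashes with the footnote only when the panel is centred low enough to omit 5000.

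**Listing.** A reader might also infer that a good assay could be refused listing because no fit exists. No section says that a missing fit means rejection. At a true LoD of 50, all replicates at the 5.4 levels are positive in 98.8% of runs; at 100, in 77.4%. That plainly supports an LoD of at most 1000. At 200 the misses are nearly always confined to the 100 level, which supports the same conclusion.

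**Choosing five levels is not in itself a cure.** This objection stands. The Table 1 panel centred on a claim of 1000 does no better than the 5.4 list, although it already contains 500 and 1000. The weakness is the absence of low levels together with five replicates.

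**The high levels are not useless.** For an assay whose LoD is above the limit they carry information. With a true LoD of 5000 and an assumed probit slope of 2.5 per log10, the asymptotic standard error of log10 LoD is 0.65 on levels up to 1000, against 0.28 on all twelve.

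**Conclusion.** The contradiction between twelve levels (60 tests) and five (25 tests) is in the current text and needs correcting. The 5.4 list adds a partial conflict and a wrong description of the dilution series. The choice of panel can move the chance of a finite probit LoD from about 0.3% to about 85% for an assay with a true LoD of 200. That contrast depends on an assumed detection curve: it persists under the shallower probit curves and narrows sharply, at LoD 500, for a very steep one.

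The harm is chiefly to the LoD estimate and to verification of the manufacturer's claim. The documents do not show that a clearly good assay would fail the 1000 limit. Nor does any single panel with five replicates per level guarantee an estimate: at a true LoD of 50, even all twelve levels give a finite fit in only about 23% of runs.

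**What to change.** State one panel in the same words in 5.4, Table 1 and 6.2.

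**For 25 tests:**
- In 6.2, replace the twelve concentrations with five, chosen as in Table 1.
- In 5.4, remove the fixed list and the description as five-fold.
- In the Table 1 footnote, require for every assay, whatever its claim, that the five levels include some below 100 as well as 500 and 1000. The set 10, 50, 100, 500, 1000 is one example: it gives about 86% at true LoDs of 500 and 1000, the same as all twelve levels. Centring on the claim must give way to this requirement.

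**For 60 tests:** keep twelve levels in 6.2, delete the five-level footnote, change the row total to 60, and align 5.4.

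In either case correct the totals in Table 1 (305) and section 10 (310): the rows sum to 298 with 25 LoD tests and to 333 with 60.

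**Cost:** wording only for the 25-test version, with less information on assays whose LoD lies well above 1000. The 60-test version needs 35 more tests than the Table 1 row lists.
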